### Ethical Considerations

To ensure that ethical standards were met, the study adhered to the principles of the Declaration of Helsinki and the guidelines of Good Clinical Practice. The Ethics Committee of the Federal University of São Paulo approved the study (A00951289489), and it was preregistered in The Brazilian Registry of Clinical Trials (RBR-4gzhy4s). Participation will be voluntary and not remunerated, and the participants will only be enrolled after providing informed consent, which has been approved by the Ethics Committee. All patient data will be safeguarded by the research team to maintain participant anonymity and confidentiality.

## Results

This trial has been preregistered in the Brazilian Registry of Clinical Trials (RBR-4gzhy4s). Recruitment started in February 2022, and by February 2024, 11 participants were enrolled in the training. Recruitment is expected to be completed by August 2024. Data analysis will be conducted between May and September 2024. The results are expected to be published in peer-reviewed journals and presented at mental health conferences after January 2025.

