**Results:**

This trial was preregistered in The Brazilian Registry of Clinical Trials (RBR-4gzhy4s). By February 2024, 11 participants were enrolled in the training. Recruitment is expected to be completed by May 2024. Data analysis will be conducted between May and September 2024. The results are expected to be published in January 2025.

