**Figure 1 figure1:**
[figure not shown]
Study design and patient flowchart. (1) We applied the informed consent form, IQ assessment, and Structured Clinical Interview for DSM-5-Research Version. (2) Participants who are deemed ineligible or unwilling to participate or continue in this study will be removed from the study. (3) We conducted baseline assessments using Measurement and Treatment Research to Improve Cognition in Schizophrenia (MATRICS), Positive and Negative Syndrome Scale, and Goal Achievement Scale. (4) We are awaiting a group of 2-3 eligible participants who have successfully completed the IQ and MATRICS assessments. (5) A 10-week training program with Feuerstein Instrumental Enrichment (FIE) will be conducted, with a frequency of 2 sessions per week. (6) A postintervention assessment will be conducted 1 week after the completion of the FIE program. (7) A follow-up assessment will be conducted 6 months after the completion of the FIE program. (8) The primary outcome of the study will be functionality, which will be measured using the Goal Attainment Scale scores. In addition, problem-solving and reasoning abilities will be assessed using the maze scores from the MATRICS assessment.

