### Analysis

Data will be analyzed using IBM SPSS (version 21) or Jamovi software following the intention-to-treat approach. The last observation carried forward will be the procedure to impute the missing data. Sociodemographic and baseline information of the patients will be described to show the sample characteristics.

The study will use ANOVA or Kruskal-Wallis tests to analyze changes in numerical variables, including primary and secondary outcomes, as well as exploratory analyses, depending on the data distribution. Post hoc pairwise comparisons will be conducted using the Bonferroni adjustment for multiple comparisons in the Friedman test. The chi-square test will be used to analyze categorical data, such as sex. The effect size will be calculated using Cohen *d*, based on the mean and SD of the mean t1 for the GAS.

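### The May–September 2024 analysis window closes before the last 6-month visits under either stated recruitment end date, and the two end dates conflict

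*Protocol article*

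**What the plan says.** The article gives two dates for the end of recruitment. The Abstract (Results paragraph) says "Recruitment is expected to be completed by May 2024"; the Results section says "Recruitment is expected to be completed by August 2024. Data analysis will be conducted between May and September 2024". The Abstract gives the same analysis window. On publication, the Abstract expects January 2025, while the Results section expects it after January 2025.

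The visit schedule is fixed elsewhere. The Intervention section sets a 10-week programme. The Figure 1 legend puts t1 one week after the programme ends, and for t2 it states: "A follow-up assessment will be conducted 6 months after the completion of the FIE program". Progress is reported as "Recruitment started in February 2022, and by February 2024, 11 participants were enrolled in the training", against a planned total of 17.

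The Analysis section follows intention-to-treat and adds: "The last observation carried forward will be the procedure to impute the missing data". It makes no exception for visits not yet due. The article describes neither a data-lock rule nor a staged analysis.

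**The concern.** A patient needs more than eight months from the first session to t2. A window that ends in September 2024 cannot hold the t2 of anyone who starts training in the spring or summer of that year. Under the Results section's date, the analysis also opens in May while entry runs on to August.

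What is at stake is the 6-month result and, under one of the two dates, part of the pre–post comparison on the goal scale for which the sample size was calculated. Missing cells created by the calendar differ from dropouts: the visit will happen, only later. If such cells were imputed by carrying forward, an unreached t2 would equal t1 and would read as maintained benefit. An unreached t1 would equal baseline and would read as no change.

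**Working it through.** The plan gives dates here and no calculated figure, so there is nothing to reproduce first. The check is calendar arithmetic.

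**Inputs**
- Programme length: 10 weeks (Intervention).
- t1 = training start + 10 weeks + 1 week (Figure 1 legend).
- t2 = training start + 10 weeks + 6 months (Figure 1 legend).
- Last entry: 1–31 May 2024 (Abstract) or 1–31 August 2024 (Results).
- Window closes: taken as 30 September 2024, the latest reading.
- Wait between entry and training: taken as zero. Figure 1 says patients wait for a group of 2–3, which can only push the visits later.

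**Visits of the last entrant**

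| Training start | Programme ends | t1 | t2 |
|---|---|---|---|
| 1 May 2024 | 10 Jul 2024 | 17 Jul 2024 | 10 Jan 2025 |
| 31 May 2024 | 9 Aug 2024 | 16 Aug 2024 | 9 Feb 2025 |
| 1 Aug 2024 | 10 Oct 2024 | 17 Oct 2024 | 10 Apr 2025 |
| 31 Aug 2024 | 9 Nov 2024 | 16 Nov 2024 | 9 May 2025 |

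The last t2 falls about 3 to 4 months after the window closes (May entry) or about 6 to 7 months after (August entry). The last t1 fits under the May date. Under the August date it is late by up to about 7 weeks (30 September to 16 November).

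**Latest training start that still fits**
- For t2: 30 September 2024 − 6 months − 10 weeks = 20 January 2024.
- For t1: 30 September 2024 − 11 weeks = 15 July 2024.

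**Patients affected at t2**
- Still to enter after February 2024: 17 − 11 = 6, and 6/17 = 35%.
- Even a start on 1 February 2024 gives t2 on 11 October 2024, so all six miss the window under either recruitment date.
- Any of the first 11 who started after 20 January 2024 would miss it too. Their start dates are not given, so 6 is a minimum if 17 are recruited.

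**Patients affected at t1**
- May date: none.
- August date: those starting after 15 July 2024. Their number cannot be derived from the article.

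**What carrying forward would do, if applied to these cells**
- t1 seen, t2 not yet due: t2 is set to t1, so the t1–t2 change is exactly 0.
- Neither seen: t1 and t2 are both set to baseline, so the t0–t1 change is exactly 0 as well.

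**The case against.** The dates stand in a status paragraph and are worded as expectations. Lock rules and staging are commonly left to the full protocol or the analysis plan, which are not shown. The imputation rule speaks of missing data, and a visit not yet due need not count as missing. That much stands: the infeasible timetable is documented, while the harm through imputation needs a further step that the article does not state.

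Three stronger readings are tempting, and the article does not support them.
- *Results will be published before the last t2.* Only the Abstract says January 2025. The Results section says after January 2025, which leaves room for a later t2 report.
- *The pre–post comparison on the goal scale is compromised.* This arises only under the August date, and only for entrants after about 15 July, whose number is unknown.
- *Recruitment will fall short of 17.* This needs a constant accrual rate. Patients train in groups of 2–3 and two groups may run in parallel, so up to 6 could train in one 10-week block. The article does not settle the matter.

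The objection does not reach the dates themselves. They are stated, they conflict with each other, and neither fits the article's own visit schedule.

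**Conclusion.** The point holds as a contradiction in the timetable. There are two recruitment end dates, and an analysis window that closes before the last t2 under both. On the planned total of 17, at least 6 patients (35%) have no t2 by 30 September 2024. That count assumes that 17 are recruited, that there is no wait before training, and that the window runs to the last day of September. A longer wait or an earlier close would make the gap larger.

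A reader might infer that the plan manufactures lasting benefit. That is conditional: it follows only if the data are closed in September 2024 and visits not yet due are treated as missing. The size of any resulting bias cannot be given, because the true course after t1 and the number of late entrants are both unknown.

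This should be fixed before the analysis. In an uncontrolled pilot, where the repair needs no change to design, endpoint or visits, it is not a fatal flaw.

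**What to change.** 1. State one recruitment end date, the same in the Abstract and the Results section.
2. Replace the calendar window by visit-based triggers: the t0–t1 analysis after the last t1, and the t2 analysis after the last t2. On the dates above, the last t1 is mid-August 2024 at the latest for May entry and mid-November 2024 for August entry. The last t2 is early February 2025 and early May 2025 respectively.
3. State that last observation carried forward is not applied to visits not yet due at the time of an analysis.

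The cost is a later report, or a two-stage report with t1 first and t2 afterwards. No extra patients or visits are needed.

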## Discussion

### Principal Findings

The FIE program is an ecological intervention that requires patients to apply strategies to solve tasks and generalize them to their daily lives. By promoting neuroplasticity, cognitive flexibility, self-awareness, and socialization, our study is designed to offer space for patients to engage in productive discussion and socialization through mediation, which may enhance patient insight into their own cognitive processes. The FIE program allows patients to build knowledge by sharing ideas with peers and mediators [21], which may improve engagement and self-esteem. In addition, cognitive abilities such as attention, visual perception, organization, and flexibility are required to perform these activities [25]. Under this intervention, we aim to challenge patients in a safe environment, creating opportunities for the generalization of real-life strategies.

The GAS assessment is a valuable tool not only for project staff to report changes in functionality but also for the patients themselves. By tracking the patient’s progress toward their own goals, regardless of cognitive changes, they can become active participants in their own recovery process. This helps to increase motivation, engagement, and self-esteem and ultimately leads to better treatment outcomes. Our goal of evaluating functionality as a primary outcome was to focus on recovery from the patient’s perspective, rather than data change, as an isolated construct.

The early years following the first episode of schizophrenia are crucial for recovery. Antipsychotic medications can improve positive symptoms, however, adherence to treatment may be highly influenced by psychological and behavioral interventions that aim to enhance insight and neuroplasticity. In addition to understanding the nature of the illness, it is important for individuals with schizophrenia to gain insight into their functional and cognitive deficits as part of the recovery process. This can help develop realistic goals and strategies to improve their overall functioning and quality of life. By recognizing and addressing these deficits, individuals with schizophrenia can play a more active role in their recovery and work toward achieving their full potential.

Professional capacitation in FIE requires intense training of the mediator, who needs to go through the experience of being mediated before becoming a mediator, using an immersive approach. Some of the FIE assumptions, such as intentionality or reciprocity and the mediation of transcendence, focus the interactions on the needs of the patient and on learning as a process that transcends the task itself. The mediator’s intentionality involves ensuring the task and the information can be effectively understood by the patient, shaping the behavior and experience to a more holistic outcome [38]. Having a person with this profile as part of a multidisciplinary team can enrich the interaction of the professional group, expanding the perspective of how the team works with the patient and the patient himself translating the knowledge for daily life behavior for the group. After having a professional trained in FIE, it becomes an accessible and low-cost intervention.

Considering the topics described above, it is necessary to explore the effects of this intervention and disseminate the results to a broader community. Given the high prevalence of schizophrenia and its associated functional impairments, comprehensive interventions such as FIE may have positive impacts on the recovery process, which are essential public health priorities, particularly in low- and middle-income countries, where access to effective treatment is often limited. If this study shows a gain in functionality, the dissemination of this technique can increase access to evidence-based treatments, ultimately leading to improved outcomes for individuals with schizophrenia.

### Limitations

The major limitation of this study is the absence of a control group, which was a decision made due to several issues recognized by the research team, including sample characteristics and the onset of the SARS-CoV-2 pandemic. The recruitment of patients after their first episode of schizophrenia within a 5-year time window posed a challenge, as many patients may have a long duration of untreated psychosis or have already had the disease for more than 5 years. In addition, some patients in remission may decline to participate in the intervention for personal reasons, such as a lack of insight into the disease or the side effects of medication, both of which can affect the willingness to participate in psychosocial interventions.

Other limitations are associated with the FIE technique. The mediator must be a specialist in the technique and trained by an authorized mentor or institution. Training a mediator in FIE is challenging not only because of its cost of nearly US $1000, equivalent to 72 hours of initial formation but also because of the need for a mediator’s constant practice in order to develop the required skills that will enable him or her to work with the sample while maintaining the focus on the FIE proposition. Nowadays, this may represent a barrier to replicating the methodology in the general medical system. However, other behavioral techniques faced the same challenges when they were first applied. An example of this was the challenges faced by applied behavior analysis (ABA) applied to autism in the 60th/70th [39]. To be an ABA specialist, someone must be trained for approximately 2000 hours [40]. In addition, the gains achieved by the patients made it the first line of intervention for this population, leading to ABA popularization [39]. Therefore, difficulties in FIE capacitation and training may exist but should not discourage the investigation of its effects on schizophrenia.

Another possible issue is patient resistance to attending the intervention twice per week. We will provide a friendly and welcoming environment for intervention and rely on the possible gains as a key to maintaining adherence and reducing dropouts. Furthermore, none of the 11 participants enrolled by now dropped out of the study.

### Conclusions

In conclusion, our project focuses on the investigation of the effects of the FIE program in patients with first-episode schizophrenia. Our results may show if this ecological approach, focused on generating insight and neuroplasticity, will impact functionality. If so, we expect to help patients become active participants in their own recovery process. Despite the limitations of this study, such as the absence of a control group and challenges associated with professional FIE training, investigating FIE intervention in first-episode schizophrenia is valuable because of the low cost of application and accessibility of this technique. Furthermore, we are exploring some gaps that still exist in the treatment of people with schizophrenia: (1) there is no effective intervention recognized as a first line to improve cognition and functionality in schizophrenia; (2) the current cognitive intervention programs in schizophrenia yield few or no effective generalizations to daily life; and (3) the importance of assessing functionality based on the patient’s own goal, as we will do with the GAS, instead of relying only on scale scores. Our research can contribute to increasing the knowledge of nonpharmacological interventions for schizophrenia.

## Abbreviations

ABA: applied behavior analysis
*DSM-5*: *Diagnostic and Statistical Manual of Mental Disorders, Fifth Edition*
FES: first-episode schizophrenia
FIE: Feuerstein Instrumental Enrichment
GAS: Goal Achievement Scale
MATRICS: Measurement and Treatment Research to Improve Cognition in Schizophrenia
MLE: mediated learning experience
PANSS: Positive and Negative Syndrome Scale
SCID-5 RV: Structured Clinical Interview for DSM-5-Research Version
SCM: Structural Cognitive Modifiability
